### Aims

This paper describes the methodology leading to the development and pilot testing of a CBT-based text messaging intervention (TXT-CBT) targeting ART adherence and drug use. Although there are features of CBT such as direct therapist feedback concerning therapy homework, for example, that cannot be replicated using a predominantly automated text messaging platform, the TXT-CBT program transports the essential features of CBT for relapse prevention to the technology-assisted platform, with recognition of these inherent limitations. Some of the limitations imposed by a technology-based approach are mitigated by the involvement of a clinician in the TXT-CBT intervention program.

The purpose of this study was to develop, with user feedback, a 12-week CBT-based text messaging treatment program targeting ART adherence and drug use and test its efficacy through a pilot randomized clinical trial. The specific aims of the study were to (1) test the impact of TXT-CBT over and above usual care for HIV on substance use and health care outcomes, (2) evaluate the differential effect of TXT-CBT versus usual HIV care on HIV risk behavior and ART adherence, and (3) examine potential mechanisms of action of TXT-CBT.

The following hypotheses addressed the goals of the study:

Among substance-dependent adults receiving HIV care, TXT-CBT would yield superior clinical outcomes relative to usual care in reducing substance use and health service utilization during and after treatment. In particular, while some health care utilization may increase among those who benefit from TXT-CBT (eg, use of routine HIV care services), we anticipate reductions in hospitalizations and emergency care services secondary to substance use.TXT-CBT would have superior effects on ART adherence and HIV risk behaviors relative to usual HIV care.TXT-CBT would have a direct effect on psychological variables that are recognized mechanisms of change in CBT treatment for addicted populations (negative affect, self-efficacy, social support). Specifically, we predicted that reductions in negative affect and cravings and increases in self-efficacy and social support would be positively associated with retention in TXT-CBT and inversely related to substance use during and after treatment.

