## Methods

### Study Design

The study began with formative research to develop the intervention. This was followed by a 2-group randomized controlled trial (RCT) in which individuals receiving usual care for HIV were randomly assigned to receive either TXT-CBT or an informational pamphlet concerning HIV and substance use. The trial was conducted and reported in accordance with the Consolidated Standards of Reporting Trials (CONSORT) guidelines [43]. Face-to-face assessments were conducted at baseline and weeks 4, 8, 12, and 24. Phone-based assessments of ART adherence were also conducted at each of these timepoints.

All study procedures were approved by the University of California, Los Angeles Institutional Review Board. This trial is registered at ClinicalTrials.gov [NCT01884233].

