### Technical Support

Participants received weekly calls from the research staff to collect qualitative data concerning the perceived helpfulness of the TXT-CBT intervention and address any technical difficulties they may have been experiencing. A research assistant reviewed the text messaging logs regularly to monitor whether text messages were being sent on time and whether participants were engaging in texting. If participants wished to disenroll from the study they could text the keyword STOP.

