#### ART Adherence

ART adherence was assessed using both phone-based UPCs and viral load data. Both home- and phone-based UPCs have been shown to be reliable and valid measures of HIV treatment adherence, yielding comparable data to electronic medication monitoring [57,58] and significant correspondence with plasma viral load [59]. At the initial research visit, participants were trained by an intake assessor and a phone-based pill counter on the telephone in procedures for conducting UPCs. Training focuses on instructing participants to organize and count their pills. The first UPC was conducted within 1 week of the training, with subsequent monthly UPCs at unannounced times during and after the intervention through follow-up at week 24. All UPCs were conducted for each ART medication the participant is taking. Pharmacy information from pill bottles was also collected to verify the number of pills dispensed between calls. A medication adherence score was then calculated as the ratio of pills counted to pills prescribed, taking into account the number of pills dispensed. Using this method, the adherence score represents the percentage of pills taken as prescribed averaged across medications [60].

Viral load served as a biological indicator of adherence. Consistent with the typical frequency with which viral load is assessed in clinical settings, data concerning viral load was collected at baseline, treatment end, and follow-up. Participants either provided us with a copy of their latest viral load results or signed a medical release of information allowing us to obtain their viral load results directly from their medical provider.

**Table 1 table1:** Key variables and measurements.

	Variables	Measurements	Screen	BL	Week 4	Week 8	Week 12	Follow-up

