**Secondary outcomes**								
	Medication compliance	Self-report^c^		x	x	x	x	x
	Behavioral strategies	Self-report^c^		x				x
	Depression	PHQ-9^c,d^		x	x	x	x	x
	Anxiety	OASIS^c,e^		x	x	x	x	x
	Drug-taking self-efficacy	Drug-Taking Confidence Questionnaire^c^		x			x	x
	Health-related quality of life	SF-12^c,f^		x			x	x
	Readiness for change	SOCRATES-D^c,g^		x				

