#### Drug Taking Self-Efficacy

Drug taking self-efficacy was measured using the Drug-Taking Confidence Questionnaire [65], which measures confidence in avoiding alcohol and other drugs (abstinence goal) or heavy use (moderation goal) across the 8 high-risk categories in Marlatt’s taxonomy of relapse precipitants [66]. Participants imagined themselves in 8 specific situations and rated confidence in resisting the urge to drink heavily or use a specific drug.

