### Statistical Analyses

Analyses in the pilot study will allow basic description of the sample in terms of distributional characteristics, variability, and missing data as well as examination of possible effect sizes in comparing the groups. Preliminary analyses will include descriptive statistics and confidence intervals, computation of scale scores, and assessment of reliability. Exploratory analyses will use a random effects regression approach to examine group differences across the repeated observations (baseline, treatment end, and follow-up) as specified in each of the study aims. This type of model accommodates the (potentially correlated) repeated measures and allows for inclusion of covariates (ie, subject characteristics on which the groups differ at admission) and additional repeated observations for some measures (eg, viral load at baseline, treatment end, and follow-up). The pilot sample size of 25 per group should allow detection of an effect size of approximately d=.7 in differential change in outcomes from baseline to follow-up, assuming a moderate correlation of 0.50 over time and allowing attrition of up to 20% (power=.80, one-tailed alpha=.05). This detectable effect size would translate to a differential change of about 19 points on the ART adherence composite score assuming an average (across time) pooled (across groups) standard deviation of about 27, as found by Safren [11] for a specialized CBT intervention for HIV-infected individuals. Safren et al found a differential change of approximately 25 points.

Separate analyses will address each measure in aims 1, 2, and 3. For example, analyses for aim 2 will include as dependent variables urine toxicology results for opioids and stimulants, ART adherence scores, health-related quality of life scores from the SF-12, and select items from the ASI indicating number of days in the past month utilizing health services. Analyses for aim 3 will include correlations between changes in self-efficacy (Drug-Taking Confidence Questionniare) and treatment retention and substance use during and after treatment.

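### Self-efficacy is first re-measured when treatment ends, so the Aim 3 correlation with in-treatment drug use cannot show direction, and the one with retention covers only people assessed at week 12 or later

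*Protocol article*

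**What the plan says.** The third hypothesis under Aims treats self-efficacy as a mechanism of change in CBT and predicts that "increases in self-efficacy and social support would be positively associated with retention in TXT-CBT and inversely related to substance use during and after treatment". Principal Findings, in the Discussion, repeats the mechanistic reading: self-efficacy is given as an example of a process expected to explain part of any effect of TXT-CBT on the clinical outcomes. Statistical Analyses turns this into "correlations between changes in self-efficacy (Drug-Taking Confidence Questionniare) and treatment retention and substance use during and after treatment".

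Study Design fixes the visits: "Face-to-face assessments were conducted at baseline and weeks 4, 8, 12, and 24". In Table 1, the row for "Drug-taking self-efficacy" is marked at baseline, week 12 and follow-up (week 24), with weeks 4 and 8 empty. The instrument is short: "Participants imagined themselves in 8 specific situations and rated confidence". Depression (PHQ-9), anxiety (OASIS), urine screens and the Timeline Followback are all marked at weeks 4 and 8 as well.

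Under Substance Use, the Timeline Followback looks back 30 days at weeks 4, 8 and 12, and 90 days at follow-up. Under Intervention Content, the messages run for 12 weeks. Technical Support says: "If participants wished to disenroll from the study they could text the keyword STOP".

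**The concern.** The article states both a measurement schedule and an analysis, and they do not fit for two of the three named correlations.

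For drug use during treatment, the proposed mechanism is first re-measured when the use it should explain is already over. A negative correlation would look like support for the mechanism, but it would arise equally if people who cut down became more confident as a result.

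For retention, a change score exists only for someone who attended at week 12 or later. Those who left the study earlier, who carry most of the information about retention, are absent from the calculation.

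At stake is the mechanism claim, which the article lists among its strengths and which could shape the larger trial it anticipates. The between-group comparisons on the primary outcomes are not touched.

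**Working it through.** **The plan's own figure.** The only power statement is d = 0.7 for differential change. With 25 × 0.8 = 20 per group, one-tailed alpha 0.05, power 0.80 and baseline adjustment at r = 0.50, the detectable d is (1.645 + 0.842) × √(1 − 0.50²) × √(2/20) = 2.487 × 0.866 × 0.316 = 0.68. The figure reproduces, but it concerns group differences and says nothing about the Aim 3 correlations.

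**Timing (Table 1, Study Design, Substance Use).**

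| Quantity | Period covered or time taken |
|---|---|
| Self-efficacy | baseline, week 12, week 24 |
| In-treatment use (Timeline Followback) | 30 days up to each of weeks 4, 8 and 12 |
| Post-treatment use (Timeline Followback) | 90 days up to week 24 |

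1. Every in-treatment Timeline Followback window ends at or before the week-12 visit, which supplies the first post-baseline self-efficacy value. Baseline-to-week-12 change therefore never precedes in-treatment use.
2. Week 12 to week 24 is 12 × 7 = 84 days. The 90-day window at week 24 reaches 90 − 84 = 6 days back into treatment. Trimmed to days after the week-12 visit, it follows the baseline-to-week-12 change in time.
3. Statistical Analyses does not fix the change interval. A baseline-to-week-24 change would bring the same problem to post-treatment use, because the week-24 rating comes after that window.

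**What reverse causation alone would produce.** The documents give no figure, so this is an assumption. Let standardised in-treatment use U lower week-12 self-efficacy with path β, with no effect of self-efficacy on use, and let the baseline rating be independent of both. The change score then has variance 2 and covariance −β with U, so r = −β/√2.

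- β = 0.3: r = −0.3/1.414 = −0.21
- β = 0.5: r = −0.5/1.414 = −0.35

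The size depends on β. The sign does not, and it is the sign that Aims predicts.

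**Retention.**

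1. If retention is scored as weeks enrolled up to 12, everyone assessed at week 12 scores 12. The standard deviation is 0 and the correlation does not exist in that group.
2. If some who left the programme are still assessed, it exists but is attenuated. In a simulation with an assumed latent correlation of 0.3 to 0.5, 20% leaving evenly over the 12 weeks, and half of them still assessed at random, r is 0.16 to 0.28. In the full sample it would be 0.21 to 0.35.
3. If retention means message exposure, it can vary among people assessed at week 12.

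**The case against.** The strongest reply is that Aims predicts associations, a correlation tests an association, and Principal Findings calls the process analyses exploratory. This is also a pilot, the change interval is not fixed, and lag details may sit in an analysis plan that is not shown. Much of that stands. It limits the importance of the point, but no choice of interval gives a self-efficacy change that precedes in-treatment use, because no such measurement is scheduled.

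Several stronger readings are tempting and are not supported:

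- **The retention correlation is undefined outright.** Retention is not defined in the article. Texting STOP is one way to leave the study; nothing says that ceasing to engage with the messages ends the separate, paid assessments. Message exposure is recorded in its own right, and someone who misses week 12 but attends week 24 still has a later change score.
- **Five of 25 TXT-CBT participants will lack a change score.** 25 × 0.20 = 5 holds only if the full allowance is used and all losses fall before week 12. The 20% is an upper allowance, stated for change to follow-up.
- **Self-efficacy is the only mechanism without an early value.** Table 1 lists no dedicated measure of craving or social support. Only negative affect has values at weeks 4 and 8.
- **Cause and effect are reversed.** Change from baseline to week 12 builds up over the same weeks as in-treatment use. Direction is ambiguous, not shown to be reversed.

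**Conclusion.** The point holds in a limited form. From the schedule alone, with no numerical assumption, the correlation of self-efficacy change with drug use in weeks 1-12 is concurrent or retrospective and cannot support the mechanistic reading given in Aims and Principal Findings. The retention correlation covers only people assessed at week 12 or later. It has little or no variation if retention means weeks enrolled to week 12, and is more informative if it means message exposure. The third correlation, with use after treatment, is correctly ordered provided the change runs from baseline to week 12.

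The values of -0.21 to -0.35 illustrate reverse causation under an assumed path and are not estimates for this trial. The consequence is confined to the interpretation of an exploratory analysis.

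**What to change.** 1. Define the Aim 3 mechanism analysis as baseline-to-week-12 change in self-efficacy against drug use after week 12, using the week-24 90-day Timeline Followback trimmed to days after the week-12 visit.
2. If the correlation with in-treatment use is kept, report it as non-directional and not as evidence of mechanism.
3. Drop the correlation of self-efficacy change with enrolment-based retention. Alternatively, use message exposure and state that the result covers only people assessed at week 12 or later.
4. Optionally, add the questionnaire at weeks 4 and 8 to the web session that already carries PHQ-9 and OASIS, for participants not yet past those visits and in the larger trial the authors foresee. Early change could then be related to later use.

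Items 1 to 3 cost wording only, since the data are already scheduled. The price is a narrower claim with modest precision. If 40 of 50 participants have both measurements, the detectable correlation at 80% power and one-tailed 0.05 is tanh(2.487/√37) = 0.39. For 20 in TXT-CBT alone it is tanh(2.487/√17) = 0.54. Item 4 may reach few participants: collection was expected to end in July 2016, and the last participant passes week 8 some 24 − 8 = 16 weeks before the final visit.

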## Results

Currently, data collection is ongoing and is expected to be completed in July 2016. We expect that analysis and results will be available by September 2016.

## Discussion

### Principal Findings

In this clinical trial protocol, we present the study design of a two-phase intervention development and evaluation project in which we (1) developed, with user input, a 12-week CBT-based text messaging intervention targeting ART adherence and drug use in an adult addicted population with HIV and (2) pilot tested the intervention in an RTC. We hypothesize that TXT-CBT will directly impact ART adherence and substance use, over and above the effect of usual care for HIV, relative to those who receive usual HIV care in conjunction with an informational pamphlet concerning HIV, ART adherence, and substance use. Exploratory analyses will be conducted to examine process changes in TXT-CBT and their associations with outcomes. We expect that mechanisms of action demonstrated in prior work examining the key ingredients of face-to-face CBT (eg, self-efficacy) will also account, at least in part, for any therapeutic effects of TXT-CBT on the target clinical outcomes in this study.

### Limitations

The major limitation of the study design is the absence of a control condition matched for time and attention. Likewise, data collection procedures that are specific to the active TXT-CBT condition, such as qualitative data collection efforts to ascertain perceived acceptability and helpfulness of the intervention, were not balanced between conditions and could potentiate the effects of the TXT-CBT intervention. Nevertheless, this initial investigation is designed to establish the acceptability and preliminary outcomes of the TXT-CBT intervention; if the current hypotheses are supported, a text messaging control condition will be developed as part of a larger, fully powered RCT. Likewise, the sample size limits the statistical power for detecting effects of the intervention; nevertheless, as a pilot trial, the proposed N is appropriate for meeting the study objectives.

### Strengths

This is the first trial to our knowledge that uses a theory-based intervention approach to the treatment of addiction via a text messaging platform. As such, rather than implementing a single behavioral strategy (eg, reminders or motivational sayings), the TXT-CBT provides a therapy program that draws its content from evidence-based addiction and medication adherence interventions. Second, we focus on a well-defined population (ie, HIV-infected adults with substance use disorders) with an urgent need for accessible, low-cost intervention approaches to reduce risk factors for the spread of HIV infection (including drug use and poor ART adherence). Third, we involved the users closely in the intervention development process to optimize the likelihood of acceptability and participant retention in TXT-CBT. Finally, by investigating mechanisms of action of TXT-CBT, this study is expected to advance our understanding of the psychological processes by which text messaging interventions effect behavior change.

### Conclusions

We present the methodology germane to the development and pilot testing of TXT-CBT, a theory-based intervention using a technology-based text messaging platform for HIV-infected adults with substance use disorders. By providing support to maximize HIV treatment regimen adherence and reinforce coping skills to prevent relapse to substance use, TXT-CBT may provide a promising, cost-effective, and easily deployable strategy for the treatment of substance users who are HIV-infected.

## Appendix

Multimedia Appendix 1 Substance Abuse and Mental Health Services Administration Pamphlet. Drugs, Alcohol and
HIV/AIDS: A Consumer Guide.

## Abbreviations

ART: antiretroviral treatment
CBT: cognitive behavioral therapy
DSM-IV: Diagnostic and Statistical Manual of Mental Disorders, 4th Edition
OASIS: Overall Anxiety Severity and Impairment Scale
OST: opioid substitution therapy
PHQ-9: Patient Health Questionnaire–9
PWID: people who inject drugs
RCT: randomized controlled trial
SEXINFO: Sexually Transmitted Infection and HIV Prevention Program for Adolescents
SF-36: 36-item Short Form Health Survey
SOCRATES-D: Stages of Change Readiness and Treatment Eagerness Scale
TAU: treatment-as-usual
TLFB: Timeline Followback
TXT-CBT: cognitive behavioral therapy–based text messaging intervention
UPC: unannounced pill counts
